### PFMT sessions

For both groups, the weekly sessions last 1 h and include a 15-min educational period and a 45-min exercise component. The educational period covers the various functions of the PFMs, including pre-contraction and normal bladder control, and voiding parameters: fluids and fluid intake; toilet positions; and voiding dynamics. The exercise component includes PFM strength, endurance, and coordination exercises. Between PFM exercises, lower extremity strength, balance and functional exercises (dance) are performed. This approach is in line with our previous research findings, which indicate that mixed and stress UI older women have reduced PFM and lower-extremity strength and balance as compared to continent women [18, 51, 52]. It is also a component of PFMT programs designed for the elderly [16, 17]. The treatment protocol is divided into three phases allowing for gradual progression in treatment; that is, the gradual addition of increasingly difficult exercises in terms of exercise duration, repetition, and position. Each phase lasts four weeks. See Table 2 for monthly treatment’s exercise details.

**Table 2 Tab2:** Monthly treatment’s exercise details

	Warm-up exercises	Pelvic floor exercises				Core exercises	Dance
		Knack^a^	Maximal contractions^a, b^	Fast contractions	Podiums^c^		
Weeks 1–4	Anterior and posterior pelvic tilts standing (4 reps), plantar flexion and dorsal flexion of the ankle (4 reps bilaterally)	(1 cough only) 3 reps	6 reps, 6-s hold	—	3 reps, 6 s/step	Pull belly button towards spine four-point kneeling (6 reps, hold 6 s), bridge (6 reps, 6 s hold)	3 beginner songs
Weeks 5–8	Simple rotation of the pelvis standing (4 reps), plantar flexion and dorsal flexion of the ankle (4 reps bilaterally)	(2 coughs) 3 reps	8 reps, 8-s hold	2 reps, 8 contractions	3 reps, 8 s/step	Pull belly button towards spine four-point kneeling + contraction of the PFM + lifting of the arm (8 reps, 8-s hold)	3 intermediate songs
Weeks 9–12	“8 shaped” rotation of the pelvis standing (4 reps), plantar flexion and dorsal flexion of the ankle (4 reps bilaterally)	(3 coughs) 3 reps	10 reps, 10-s hold	2 reps, 10 contractions	3 rep, 10 s/step	Pull belly button towards spine four-point kneeling + contraction of the PF+ lifting of one arm (8 reps, 8-s hold), contraction of PFM+ contraction transverse + bridge (6 reps, 8-s hold)	3 advanced songs

^a^The knack involves pre-contracting the PFM before and during a cough

^b^The maximal contractions: is done through different positions depending on the week

^c^Podium exercise (moderate-maximal-moderate contraction): can be inverted depending on the week

*Reps* repetitions, *s* seconds, *PFM* pelvic floor muscle

For the individual treatment group, the pelvic floor exercises: can be done with a biofeedback probe depending on the week

#### Individualized PFMT

The only specificity of this treatment group is that women participate in one-on-one, 1-h sessions with intra-vaginal electomyography (EMG) biofeedback under the supervision of an experienced physiotherapist. This treatment approach is in line with clinical practice in Canada [53].

#### Group-based PFMT

The only specificity for this treatment group is that women participate in groups of eight in a weekly 1-h session, under the supervision of an experienced physiotherapist. They are also offered up to three optional private (20 min) sessions with the physiotherapist leading their group (either before or after a group session) to ensure understanding and correct performance of a PFM contraction – as confirmed by vaginal digital palpation [17]. This treatment approach is consistent with Bo’s PFM exercise class [54] and our more recent pilot cohort studies indicating it is both feasible and effective intervention for UI in aging women [18, 55]. In case of slow recruitment, we have established a minimum group size of six participants in order to avoid delays for those assigned to group physiotherapy.

### Home PFMT program

Women in both groups are expected to perform PFM strengthening, endurance, and coordination exercises at home, five days a week, for the duration of the treatment [18, 22, 51, 55]. To support progression in the treatment, the home exercise program parallels the three phases in the treatment protocol with the gradual addition of increasingly difficult exercises every four weeks. To standardize home PFM exercises, each participant is given a PFM exercise diary describing the home PFMT exercises, in which they can record their adherence to the home program. Finally, all participants are asked to refrain from seeking other forms of treatment (such as medication or surgery) during the study.

### Standardization of treatment

Physiotherapists who deliver the interventions are extensively trained in standardized treatment protocols and rigorous procedures to conduct both individualized and group-based PFMT. Each physiotherapist participates in a 4-h training workshop, is given a written a treatment protocol with checklist, and is individually supervised for three to six treatments. Routinely, during the course of the study, all physiotherapists come together with the study team to ensure that consistency in the protocol is being maintained and to discuss concerns that may arise. For physiotherapist effect not to confound results, the same physiotherapist is conducting both individualized and group-based PFM training in a single location.

#### Intervention allocation

A research assistant (one in each center) communicates with the CRIUGM IT service analyst to get the next sequential allocation and inform the participants as to which treatment they have been allocated and, in addition, organize the logistics of the PFMT intervention.

#### Blinding

Investigators, data analysts, and physiotherapists in charge of outcome evaluations remain blinded to the individual participants trial group allocation. Although participants cannot be blinded to their own group allocation, they are blinded to the study’s hypothesis and to the treatment offered in the alternate group. Despite their different formats, both groups have parallel weekly sessions in terms of content and time, but at different locations and/or on different days. To minimize the risk of assessor’s unblinding, participants are asked (both in the consent form and at the time of each assessment) not to discuss their treatment with the independent assessor. In addition, in each center, the assessment is separated from the intervention session, by both time and location.

### Outcome measures and moderators/confounders

#### Primary outcome measure

The primary outcome measure is the mean percent reduction in the total number of UI episodes one year post randomization, as measured by a seven-day bladder diary [28]. For example, a participant experiencing four leaks per week pre intervention and two leaks per week at the one-year follow-up would be considered to have had a 50% reduction in leakage episodes. The number of leaks (as measured by the seven-day diary) is considered one of the most reliable measures of success for incontinence treatment and has been widely used in this type of research [16, 28, 44, 47, 51]. Moreover, the reduction in the number of daily leaks, expressed as a percentage, is information that can be easily understood by participants in pre-treatment counseling. As a measurement tool, the seven-day diary has a high compliance rate and good reproducibility [28, 56].

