### Onsite eligibility evaluation (1 h)

Women are scheduled for onsite evaluations with a physiotherapist if they report at least three UI episodes on the seven-day bladder diary. After signing the consent form, the Mini-Mental State Examination [48] questionnaire is completed (excludes women with cognitive impairment) and a vaginal exam is conducted to identify any perineal pain or prolapse likely to interfere with either the evaluation or the intervention. Those not eligible for the present study are referred back to their healthcare provider. Eligible participants complete the evaluation and are randomized to either individualized or group PFMT.

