To err on the conservative side, we relied on the “standard” 95% CI, which corresponds to a stringent one-tailed type I error rate of α = 0.025 (2α = 1–0.95 = 0.05). Similar to other recent non-Inferiority trials (e.g. [70, 71]) and CONSORT guidelines [68], for the purpose of sample size calculation, we assume that the true difference between the mean reductions (%) achieved by the two interventions will be zero (i.e. that they are equally effective). Note that this assumption of equivalence of the two interventions being compared in our trial is consistent with both (a) clinical expectations and (b) (limited) published evidence concerning young and middle-aged UI women [72–74]. Finally, both published trials, which evaluated similar interventions in older women, reported within-group standard deviations (SD) of the individual % reduction scores of about 27% [44, 75]. Accordingly, we assumed SD = 27% in our calculations.

Under the above assumptions, we estimated the sample size needed to ensure high (90%) power to demonstrate the non-inferiority of the group-based intervention (assuming, as mentioned above, that the true difference is 0%). Thus, we calculated N, for which the probability that the upper boundary of the two-tailed 95% CI for the difference in the mean relative reduction (Individual – Group) excludes the “upper threshold of non-inferiority” (10% difference), will reach at least 90%. The sample size calculations were performed using the program in the PASS software package, designed specifically for power/sample size estimation for non-inferiority trials [76]. Under the assumptions outlined above, we will need 155 participants per group, for a total of 310 individuals. We also need to account for possible losses to follow-up, as we expect a 15% attrition rate by the end of the one year, based on both our pilot data and similar published trials [16, 17, 22, 51]. Thus, we will recruit an additional 54 participants per group, increasing the total number of participants to 364 (364*(1–0.15) = 310).

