Analyses for the primary outcome at one year (and secondary outcomes): The primary analysis will test our main hypothesis that group-based classes are not inferior to individualized treatment with respect to the primary outcome of relative (%) reduction in the number of leakages at one year post randomization. (For all outcomes, the analyses outlined below will be repeated using data on post-intervention assessment.) As recommended for non-inferiority trials, the hypothesis of non-inferiority will be accepted if, and only if, the upper bound of the two-tailed (1-2α) 95% CI (corresponding to a conservative Type I error of 0.025 for the one-tailed independent-group t-test) for the mean difference (in % reduction) excludes the non-inferiority threshold [68], set at 10% difference. This basic analysis will be extended to multivariable analyses. Specifically, two multivariable linear models, of increasing complexity, will be used to adjust the estimated difference between the % reduction at one year in the two groups for, respectively, (1) only the two stratification variables (center and type of UI), as well as the baseline number of UI episodes (to account for regression to the mean phenomenon); and (2) (if necessary) in addition to variables in model (1): any variable, for which a clinically important imbalance between the two arms is revealed by descriptive analyses (see above). In both models, the two-way interactions between the trial arm and (a) center and (b) UI type, will be tested using 1-df model-based F-tests to verify if the difference between the effects of the two interventions depend on either of those stratification variables. In the case of a statistically significant interaction (*p* < 0.05 for the F-test), the intervention effects will be estimated and tested separately in the respective subgroups [79]. The results of multivariable linear regression analyses will be summarized in terms of adjusted mean difference between the outcomes in the two trial arms, together with the 95% model-based CIs. In sensitivity analyses for primary and secondary outcomes at one year, ITT analyses will be conducted, using the same statistical methods.

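### The primary percent-reduction score has a ceiling but no floor and a denominator as small as three leaks, so a few low-baseline women who worsen can weigh heavily on the non-inferiority result; a supportive count analysis should be prespecified

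*Protocol article*

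**What the plan says.** All references are to the protocol article.

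- **Primary outcome measure:** "The primary outcome measure is the mean percent reduction in the total number of UI episodes one year post randomization". The worked example, four leaks falling to two, "would be considered to have had a 50% reduction in leakage episodes". The score is thus computed per woman and then averaged.
- **Onsite eligibility evaluation:** women are scheduled "if they report at least three UI episodes on the seven-day bladder diary". The smallest denominator is therefore three.
- **Sample size calculation:** two published trials "reported within-group standard deviations (SD) of the individual % reduction scores of about 27" percent. "Accordingly, we assumed SD = 27% in our calculations". The 95% CI "corresponds to a stringent one-tailed type I error rate of α = 0.025", the target is the "sample size needed to ensure high (90%) power to demonstrate the non-inferiority of the group-based intervention", and the result is 155 evaluable women per arm.
- **Data analysis:** non-inferiority is accepted only if the upper confidence limit for the mean difference (individual minus group) "excludes the non-inferiority threshold [68], set at 10% difference". The same section plans a Shapiro–Wilk check with a logarithmic, Box-Cox or non-parametric transformation if normality is violated, and extended linear models that include baseline episodes.
- **Trial management:** outliers are looked for as possible data errors. No rule is given for true extreme values.

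**The concern.** The score is 100 × (baseline − one-year count) / baseline. A cure gives +100 and nothing can exceed that, but there is no floor. At a baseline of three, each leak at one year is worth 33 points: 3 to 6 leaks scores −100, 3 to 12 scores −300. A mean and SD built from such ratios give large leverage to women with small denominators who get worse, and these are not necessarily the women with the most severe incontinence.

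Two things are at stake. A truly non-inferior group programme could fail because of very few diaries. And the power rests on a single SD value for a score whose SD is itself sensitive to those diaries.

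**Working it through.** **Inputs.** From the article: margin 10, SD 27, true difference 0, one-sided α 0.025, 155 per arm, minimum baseline 3. Assumed, because the article does not give it: mean reduction 70 in both arms, varied from 50 to 80.

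**1. The plan's own figure.** Normal approximation: n = 2 × 27² × (1.960 + 1.282)² / 10² = 153.2, so 154 per arm. With the noncentral t, power is 0.8997 at 154 and 0.9015 at 155. The stated 155 is right.

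**2. Leverage of one woman.** With an observed difference of 0, SE = 27 × √(2/155) = 3.067 and the upper bound is 1.968 × 3.067 = 6.03, so non-inferiority is shown.

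Now let one of the 155 group-arm women go from 3 to 12 leaks (−300):
- difference = (70 + 300)/155 = 2.39
- group SD = √[(153 × 27² + (154/155) × 370²)/154] = 40.1
- upper bound = 2.39 + 1.968 × √[(27² + 40.1²)/155] = 10.03

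Upper bound by size of worsening, other women showing zero difference:

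| One group-arm woman | Mean 70 | Means 50 to 80 |
|---|---|---|
| 3 to 6 leaks | 7.5 | 7.3–7.6 |
| 3 to 9 | 8.7 | 8.4–8.8 |
| 3 to 12 | 10.03 | 9.7–10.2 |
| 3 to 13 | 10.5 | 10.2–10.7 |
| 3 to 15 | 11.5 | 11.2–11.7 |

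If the other women already favour individual treatment by 2 points, 3 to 9 leaks is enough (10.4–10.8). At 3 points, 3 to 6 is enough (10.3–10.6). In the individual arm, a score of −300 gives −2.39 + 7.64 = 5.25, which does not flip the verdict.

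**3. Power.** At 155 per arm (noncentral t), with the evaluable number that would restore 90%:

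| SD | Power | n per arm for 90% |
|---|---|---|
| 27 | 0.90 | 155 |
| 30 | 0.83 | 190 |
| 35 | 0.71 | 258 |
| 40 | 0.59 | 337 |

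The 155 is the plan's own t-based figure; the other three use the normal approximation.

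In simulation (20,000 trials, beta-distributed scores, mean 70, SD 27, no true difference), adding on average one worsener per arm in both arms lowered power from 0.90 to 0.73 if she scores −200 (SD about 34), 0.62 at −300 (SD 40) and 0.53 at −400 (SD 46). How often such women occur is an assumption.

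**4. The plan's safeguards.**
- Log and Box-Cox are undefined for zero or negative scores, which are the cases at issue. A shift or a rank-based transformation would be computable, but the 10-point margin is set on the percent scale and none is given on another scale.
- Linear adjustment of the percent score for log baseline hardly changes the SE: 3.86 to 3.84, 5.27 to 5.16, 5.49 to 5.43 and 4.25 to 4.20 in four simulated settings.
- The outlier check targets data errors, so a true worsener stays in.

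**5. Does a count model do better?** It depends on the diaries. With overdispersed counts and a baseline log-SD of 0.6 to 0.8, its SE was about 8 to 23% smaller than that of the planned analysis. With Poisson counts and log-SD 1.0 it was up to about 14% larger. It resists the low-baseline case: one group-arm woman going from 3 to 12 leaks flipped 6–12% of passing verdicts, against 44–55% for the t-test. It is weaker for a heavy leaker: 30 to 60 leaks flipped 47–79%, against 13–22%.

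**The case against.** The strongest defence is that SD 27 is the SD of this same kind of score, reported by two trials of similar interventions in older women. It is a total SD, so it already contains diary noise and whatever worsening those trials saw. One of the two is also cited under Participants for the three-per-week entry indicator. Nothing in the article suggests an SD above 27. This stands: the value is supported, and what remains is that power is sensitive to it and no range is shown.

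The one-woman flip is also an edge case. It needs the group arm, a minimum baseline and a fourfold rise in leaks. At assumed means of 50 or 60 the 3-to-12 case still passes (9.74 and 9.88). This stands too, and the conditions belong in the statement of the point.

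A count model is a different estimand. The 10 points were set for the difference in mean percent reduction, the article gives reasons for the percent score, and recruitment already stood at 353 of 364. This is a good reason not to replace the primary analysis. It is no reason against a supportive one.

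Finally, supportive analyses and handling of extremes are often left to the SAP, which is not shown. But the article itself fixes the unbounded score, the margin and the transformation rule, and that rule would move the primary test off the margin's scale.

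**Conclusion.** The point holds as one of fragility, not of error. The primary score lets a few low-baseline women who worsen carry heavy weight, and the safeguards in the Data analysis section do not resolve this. In the plan's own setting, with an assumed mean of 70 and otherwise zero difference, one group-arm woman reaching about 12 to 13 leaks from 3 takes the bound from 6.0 to about 10. Milder worsening suffices only when the result already leans towards individual treatment. The consequence shown is mainly lost power; no inflated risk of falsely claiming non-inferiority has been shown.

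Three stronger readings are tempting and not supported:
- **Any single worsening woman overturns the verdict.** She does so only under the conditions above.
- **SD 27 is wrong, or diary noise alone pushes it higher.** The SD is sourced. In simulations with Poisson diaries and no between-woman variation it was 18 to 26. Values above 27 needed added between-woman variation, which is assumed.
- **A count model should be primary.** It changes the estimand, moves the sensitivity to heavy leakers, and its precision gain depends on diary variability.

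**What to change.** 1. Keep the mean percent reduction as the primary outcome, tested on its original scale. State that a failed normality test does not move the primary non-inferiority test to a scale on which the 10-point margin is undefined.
2. Before unblinding, prespecify a supportive non-inferiority analysis of the one-year leak count: quasi-Poisson or negative binomial regression with log baseline count, centre and UI type, and robust SE. Express it per arm as 100 × (1 − standardised mean one-year count / pooled mean baseline count), and show the difference with its 95% CI beside the primary result against 10 points.
3. State that this is a different estimand giving heavy leakers more weight, that it is itself sensitive to a heavy leaker who worsens, that its precision gain depends on diary variability, and that the 10-point margin was set for the mean of individual percentages.

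Agreement of the two results would indicate that the verdict does not rest on a few low-baseline diaries. Disagreement would show the reader where to look.

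The cost is some SAP wording and one extra model, with no new data. The downside is a second figure that can differ from the first and must be explained.

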#### Secondary outcome measures

Several secondary outcomes are assessed in this study, in line with the recommendations of the 4th International Consultation on Incontinence [57] and the International Continence Society [58]. For each outcome, we have selected measurement instruments that have highest psychometric properties (validity, reliability, and response to change).
*The seven-day bladder diary:* The number of micturition per day/night is monitored to document lower urinary frequency during the day and nocturia [28].
*The 24-h pad test:* This is a validated measure of quantity of urine leakage in 24 h, as measured by the weight of the pads used during a 24-h period minus the weight of the pads before the test. It is identified as a realistic appraisal of the typical urine loss during ordinary daily activity [29]. The upper limit of “normal” for the 24-h pad test has been defined for continent women as being 1.3 g [47].
*The International Consultation on Incontinence Questionnaire (ICIQ) modules:* Five ICIQ modules, known to provide brief and robust measures of UI symptoms, quality of life, and outcome of treatment are used [32].i.
*The ICIQ-Urinary Incontinence short form:* a four-item questionnaire which evaluates the impact of symptoms of incontinence on quality of life and outcome of treatment (0–21 overall score, with greater values indicating increased severity) [30].ii.
*The ICIQ-Nocturia:* a two-item questionnaire which evaluates the impact of symptoms of nocturia on quality of life and outcome of treatment (0–8 overall score, with greater values indicating increased symptom severity) [31].iii.
*The ICIQ-Vaginal Symptoms:* a 14-item questionnaire which evaluates the impact of vaginal symptoms and associated sexual matters on quality of life and outcome of treatment (0–53 vaginal symptoms subscale, 0–58 sexual matters subscale, 0–10 overall impact on quality of life subscale; with greater values indicating increasing problems) [33].iv.
*The ICIQ-Female Lower Urinary Tract Symptoms sex:* a four-item questionnaire for evaluating sexual matters associated with female lower urinary tract symptoms (0–14 overall score, with greater values indicating increasing problems with sexual matters) [34].v.
*The ICIQ-Lower Urinary Tract Symptoms quality of life:* a 20-item questionnaire which evaluates quality of life in urinary incontinent patients (0–14 overall score with greater values indicating increasing problems). The ICIQ-LUTSqol provides a detailed and robust measure to assess the impact of urinary incontinence on quality of life with particular reference to social effects [32].

*The geriatric self-efficacy index:* A 20-item instrument that enables measurement of whether a person is confident in their ability to prevent urine loss. It has been shown to be a reliable and valid instrument in the aging female population with UI [35].
*The Broom self-efficacy index (Part A):* A 14-item questionnaire to evaluate women's confidence in performing pelvic floor muscle exercise [36]. The Broom self-efficacy index has solid psychometric properties and is a useful tool to measure self-efficacy in doing PFM exercises [59].
*Patient global impression of improvement PGI-I:* a single-item global index used to measure improvement in urinary continence following PFMT on a 7-point scale that ranges from “very much better” to “very much worse.” The PGI-I has shown acceptable convergent and discriminant validity for measuring outcomes in studies of behavioral treatment for UI [37, 60].
*Satisfaction with treatment:* A single-item tool was used to document and capture perceived satisfaction with treatment: “satisfied” (does not need other treatments); “unsatisfied” (would like another treatment for UI) [17].
*PFM strength, morphometry and function:*
i.
*PFM strength on Oxford scale (digital palpation):* The Oxford scale is a 5-point scale used for PFM strength assessment amongst physiotherapists. Laycock and Jerwood have established intra-therapist reliability of this scale, tested in bent-knee lying [38, 61].ii.
*PFM function:* An intravaginal dynamometric speculum, designed by members of our research team is used to measure passive (tone) and active forces (strength), speed of contraction, coordination with cough and endurance [39]. This instrument has been widely assessed for its psychometric properties including its reliability, validity, and responsiveness [39, 62].iii.
*PFM Morphometry:* A Siemens Acuson Antares system with a 3–5-MHz curvilinear 3D/4D probe (in Montreal) and a GE Voluson Expert system with a 2–6-MHz curvilinear 3D/4D probe (in Sherbrooke) is used to evaluate several morphometric parameters at rest, during PFM contraction and on effort (cough and Valsalva): levator hiatus area and diameter, bladder neck position and displacement as well as levator plate height, using a validated and reliable methodology [40, 63, 64].

*The modified Dowel-Bryant Incontinence Cost index*

